### Study design

This is a patient-assessor blinded, randomized, sham-controlled efficacy trial on TEA for alleviating FEMA after PFP. A total of fifty-six eligible participants will be recruited from the inpatient and outpatient departments of the First Affiliated Hospital of Zhejiang Chinese Medical University. They will be assigned randomly into either the TEA or STEA group. Patients in both groups were given TEA (for TEA group), or STEA (for STEA group), and traditional acupuncture treatments (for both groups) for eight weeks. Regular follow-up will be conducted for up to four weeks after the intervention.

B-mode ultrasonography will be used to assess the changes in facial expression muscle thickness ratio of the affected/healthy side at baseline and 10 weeks after screening as the primary outcome. House-Brackmann Grade (H-B Grade) [24] and lip mobility score [25] will also be measured and analyzed at baseline and 4, 8, 10, and 12 weeks after screening, as secondary outcomes (Figs. 1, 2). The study protocol was approved by the Ethics Committee of the First Affiliated Hospital of Zhejiang Chinese Medical University on the Use of Human Subjects for Teaching and Research (approval No.2020-K-084–01) and registered in the Chinese Clinical Trial Registry (ChiCTR1900027170). The study design followed the Standard Protocol Items of Recommendations for Interventional Trials (SPIRIT) Checklist (Additional file 1).

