#### Secondary outcome measures

House-Brackmann Grade, the severity of facial paralysis will be assessed using the HB Grade at weeks 0, 4, 8, 10, and 12. Grade I (normal function) to VI (total paralysis) will be evaluated based on the facial function at rest and with effort.Lip mobility score. Lip mobility will be assessed using the lip-length index (LL-index) and snout index (S-index) at weeks 0, 4, 8, 10 and 12. The LL-index will be calculated by determining the percentage change in lip length between grinning and resting. The S-index will be calculated by determining the percentage change in lip length between puckering and resting. Lip length will be measured by determining the inter-commissural length.

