### Data processing and statistical analysis

Following the intention-to-treat principle, data processing and analysis will be performed at the Clinical Evaluation and Analysis Centre of The First Affiliated Hospital of Zhejiang Chinese Medical University. These analyses will be performed on the base of a full analysis set (FAS) and a per-protocol set (PPS). All efficacy analyses will be performed using a FAS, which will consist of all patients who passes the randomized stage and who receives at least one intervention. Last observation carried forward (LOCF) analysis will be used for missing data imputation. The PPS will be considered as a supportive analysis. The results of FAS and PPS analyses will be compared to ensure that the results are consistent. A generalized linear mixed-effect model will be used for sensitivity analysis via the PPS. A subgroup analysis will be conducted following the Kellgren–Lawrence grade.

Quantitative results will be described by the mean, standard deviation, median (quartile 3–1, Q3–Q1), minimum, and maximum, while qualitative results will be expressed as total number and percentages. Grade results with rank meaning will be described via both quantitative and qualitative methods.

The chi-square test will be used to compare the primary outcomes between the two groups. The Wilcoxon rank-sum test will be used to compare ranked data and the independent samples t-test for secondary outcome measures to analyze continuous variables. The incidence of adverse events will be determined and compared between the two groups for safety outcomes. A p-value of <0.05 will be considered statistically significant. SPSS Statistics V.22.0 will be used for all analyses. An interim analysis will be conducted when 50% of the randomized patients completed the primary outcome measurement.

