## Discussion

Acupuncture is widely used to treat PFP after the acute stage in China [27–29]. It is commonly used to treat FEMA after PFP. However, many patients find it difficult to adhere to it since it requires about three treatments per week. TEA is a new type of acupuncture with a low treatment frequency (once a week). The suture threads, such as polyglycolic acid which has good biodegradability and biocompatibility [30], are widely used in TEA in China. The TEA-embedded thread can increase the tensile strength and stimulate myoblast formation in connective tissues [21, 31], which is considered to be the basis for the clinical application of this treatment.

Herein, STEA is used to determine the effect of specific intervention factors. STEA will be applied to minimize the needle insertion effect since the penetration of traditional acupuncture can be used to treat muscular atrophy. Participants, assessors, and statisticians will be blinded to the groups to minimize comparison bias.

B-ultrasonography is widely used to measure muscle or other soft tissues and disease diagnosis [32]. It is a sensitive detection method for facial muscle thickness and safe, non-invasive, simple to operate, and cost-effective [33–35]. Studies have shown that normal humans have no significant differences in bilateral expression muscle thickness [36, 37]. Therefore, the thickness of healthy facial expression muscles can be used to detect the atrophic facial expression muscle side. Herein, the test was performed at weeks 0 and 10. The final test will be set at two weeks after treatment because improvements of the muscle structure and strength need a long time for recovery.

Moreover, facial expression muscle function recovery is essential for the evaluation of FEMA treatment using TEA. The physical functions will be assessed via H-B Grade and lip mobility score as the secondary outcome measures.

However, this study has some limitations since it is not designed for a stratified study. There are differences in FEMA recovery after PFP with different disease courses. Stratified observation can screen out the best efficacy group with certain disease courses, giving accurate guidance of TEA timing for clinical treatment of FEMA after PFP.

In summary, this study will evaluate the efficacy and safety of TEA for FEMA after PFP. These findings will enhance understanding of TEA as a therapeutic option for FEMA patients after PFP.

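### The unqualified p<0.05 rule covers secondary outcomes tested at four visits, so an isolated chance result could be called significant; the primary error rate is not affected

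*Protocol article*

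**What the plan says.** Secondary outcome measures (protocol article) defines three functional measures. For House-Brackmann grade, "the severity of facial paralysis will be assessed using the HB Grade at weeks 0, 4, 8, 10, and 12". For the lips, "Lip mobility will be assessed using the lip-length index (LL-index) and snout index (S-index) at weeks 0, 4, 8, 10 and 12". Study design goes beyond measurement: the two outcomes "will also be measured and analyzed at baseline and 4, 8, 10, and 12 weeks after screening, as secondary outcomes". The Abstract gives the same schedule.

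Data processing and statistical analysis names the tests: "The Wilcoxon rank-sum test will be used to compare ranked data and the independent samples t-test for secondary outcome measures to analyze continuous variables". The only longitudinal method is a supporting one: "A generalized linear mixed-effect model will be used for sensitivity analysis via the PPS". The threshold sentence is general: "A p-value of <0.05 will be considered statistically significant". It is not limited to the primary outcome, and nothing in the section marks the secondary p-values as nominal or exploratory. The primary outcome, by contrast, has a single post-treatment time point, week 10.

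**The concern.** A rank-sum test or an independent-samples t-test uses one value per patient. Applied to an outcome analysed at four post-baseline visits, it gives four tests per measure. With three measures and one flat threshold, any one of these results may be reported as a statistically significant difference in facial function.

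This matters because the primary outcome is muscle thickness, so whether function improves is answered only by the secondary measures. The Discussion gives them weight, saying that "facial expression muscle function recovery is essential for the evaluation of FEMA treatment using TEA". If thickness did not differ between arms, a single chance result on one lip index at week 4 or week 12 could still, under the plan as written, be called significant. If thickness did differ, the same chance result could be read as confirming that the gain carries over to function.

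**Working it through.** **The plan's own figure.** The article states no family-wise error rate. The only related figure it gives is the sample size, which shows what its alpha means. With SD 23.30, difference 21.54, alpha 0.05 and power 0.90 (Sample size section):

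n = 2 × 23.30² × (1.960 + 1.282)² / 21.54² = 24.59, rounded up to 25; 25 / 0.90 = 27.8, rounded up to 28 per arm.

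This reproduces the stated 28. The formula uses Z at α/2, so 0.05 is two-sided there. The significance sentence does not state sidedness, and two-sided is assumed below.

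**Number of tests.** Baseline is left out because a comparison at week 0 says nothing about treatment.

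- Three measures × four visits (weeks 4, 8, 10, 12) = 12.
- If LL-index and S-index are combined into one lip mobility score: 2 × 4 = 8.

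**Independence bound, no true effect, each test at two-sided 0.05.**

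- 12 tests: 1 − 0.95¹² = 0.460.
- 8 tests: 1 − 0.95⁸ = 0.337.
- 3 tests (one visit only): 1 − 0.95³ = 0.143.
- At least one of 12 favouring TEA: 1 − 0.975¹² = 0.262.

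**Correlated tests.** Results on the same patients are correlated, so independence overstates the rate. The article gives no correlations, and those below are assumptions. Null test statistics were simulated as multivariate normal, with equal correlation between visits and equal correlation between measures, and a critical value of 1.96. Chance of at least one p<0.05 among 12:

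| Between visits | Between measures 0 | 0.3 | 0.5 | 0.7 |
|---|---|---|---|---|
| 0.5 | 39.9% | 38.3% | 35.6% | 31.5% |
| 0.7 | 34.2% | 32.8% | 30.2% | 26.5% |
| 0.8 | 30.6% | 29.2% | 27.0% | 23.2% |
| 0.9 | 25.5% | 24.4% | 22.5% | 19.5% |

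Over the same grid, the chance of at least one false result favouring TEA runs from about 10% (correlations 0.9 and 0.7) to about 22% (0.5 and 0).

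**Check with the named tests.** Simulating 28 patients per arm, with t-tests for two continuous indices and a rank-sum test on a five-level grade, gave 38.9% (between visits 0.5, between measures 0.3), 33.5% (0.7, 0.3), 29.4% (0.8, 0.3) and 27.6% (0.8, 0.5). These agree with the table.

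**Smaller families.** With 8 tests the rate is 20.0 to 28.7% for visit correlation 0.5 to 0.8 and between-measure correlation 0 to 0.5. With three measures at one visit it is 11.0 to 13.6% for between-measure correlation 0.7 to 0.3. Naming a visit alone therefore does not bring the family to 5%; an order of testing or an adjustment is also needed.

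**The case against.** The strongest reply is that this is ordinary for outcomes labelled secondary. The article ranks the thickness ratio as primary and lists function as secondary throughout. The Discussion sentence on the importance of function is followed directly by one that assigns it to the secondary measures. The article also uses the language of exploration for the trial as a whole. Multiplicity handling for secondary outcomes is commonly left to an analysis plan, which is not shown, so its absence alone is no fault.

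Much of this stands. A reader might infer that the trial's type I error is inflated; it is not, because the secondary tests lie outside the primary comparison. A reader might also infer that the article makes a separate confirmatory claim for function; it states none. What remains is a rule that the article does state: it names the tests, analyses the outcomes at four visits and applies one threshold without limit. A later hierarchy would have to narrow that published sentence.

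Two further objections are fair. The count of 12 is an inference. The analysis section does not say that a test is run at each visit, and the schedule phrase includes baseline. It is still the natural reading of outcomes analysed at those weeks with two-sample tests. It is also tempting to quote a single figure of about 30%, but that needs correlations the article does not supply, so only a range can be given.

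**Conclusion.** The point holds as a moderate one. As written, the plan allows any secondary comparison below 0.05 to be called statistically significant. Under the 12-test reading, the chance of at least one nominal false positive is about 19 to 40% for assumed correlations of 0.5 to 0.9 between visits and 0 to 0.7 between measures, and 46% if independent. The chance of one that favours TEA, which is the more harmful error, is about 10 to 22%. Under every count and correlation tried, the two-sided rate is above 5%, so the direction does not depend on the assumptions, though the size does. The primary comparison's error rate is not affected.

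**What to change.** In Data processing and statistical analysis:

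1. Restrict the p<0.05 significance statement to the primary comparison. Report all secondary comparisons as exploratory, with estimates and 95% confidence intervals.
2. If a functional claim is wanted, instead pre-specify one deciding visit and a fixed order of the three measures, before any unblinded look. The choice of visit and order is the sponsor's. The interim analysis is planned when half the randomised patients have the primary measurement, and the article reports ten patients under treatment out of 56 planned, so on that status there was still time to set this first.
3. For LL-index and S-index, replace the separate unadjusted t-tests by one repeated-measures mixed model per index on the full analysis set, adjusted for the week-0 value already collected. This uses the visits together and accounts for baseline. It does not control multiplicity by itself, so item 1 or 2 is still needed.

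The cost is a few sentences, with no extra patients, visits or measurements. The small downside is that an isolated significant result at one visit can no longer be presented as a confirmed effect.

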### Data monitoring and trial steering committee

A data monitoring committee (DMC) with members from the Clinical Evaluation and Analysis Centre of The First Affiliated Hospital of Zhejiang Chinese Medical University regularly meet to monitor the study data. The DMC will monitor the overall quality and integrity of the data, examine the original CRFs, interview the researchers, verify the record of adverse events, perform an interim analysis, and confirm that the study conforms to the principles of this protocol. A Data and Safety Monitoring Board (DSMB) was also set up to monitor the performance and safety of the trial, which is composed of 5 experts from different fields of the First Affiliated Hospital of Zhejiang Chinese Medical University to ensure the safety of this trial every 6 months. The DMC and DSMB are independent of the trial researchers and have no competing interests. DSMB will reveal a participant’s allocated intervention and make the final decision on whether to terminate the trial. The First Affiliated Hospital of Zhejiang Chinese Medical University will verify participant enrolment, consent, and costs.

### Follow-up

There will be two times of follow-ups after the intervention period. The researchers will contact the participants via phone or WeChat app for successful follow-up.

### Adverse events

Adverse events (AEs) for acupuncture refers to the occurrence of symptoms or diseases that inhibit the purpose of treatment during or after acupuncture treatment. All AEs associated with TEA or acupuncture will be reported to the researcher by the participants or observed by the researcher. The description of AEs will include, time of occurrence, location of the reaction, level of severity, corresponding management and the necessity for patient withdrawal from the trial. AEs of TEA or acupuncture will be classified as local or systemic reactions according to their location.

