### Concurrent treatment

In China acupuncture has been historically used to treat sequelae after facial paralysis. And research has showed that acupuncture treatment was effective in improving sequelae of facial paralysis [13, 26]. It is highly accepted by most of the patients. So traditional acupuncture will be used as a concurrent treatment for both groups twice a week for eight weeks to improve adherence to the intervention. Moreover, acupuncture treatment will be performed immediately after TEA or STEA treatments. A 0.25*40mm disposable acupuncture needle (Jiachen Acupuncture Medical Equipment co. LTD, Jiangsu, China) will be inserted to a depth of 5 mm and retained for 30min in the following 10 acupoints (Table 1): GB20, LI4, LR3, GB12, ST7, SI18, LI20, BL2, SJ23, ST4.

**Table 1 Tab1:** Location of the acupoints

Acupoint (standard abbreviation/Chinese nomenclature)	Location
GB20/Fengchi (Affected side)	In the anterior region of the neck, inferior to the occipital bone, in the depression between the origins of sternocleidomastoid and the trapezius muscles
LI4/Hegu (Bilateral Extremity)	on the highest point of the fleshy joining between the index and thumb fingers when they are stretched outwards
LR3/Taichong (Bilateral Extremity)	In the depression anterior to the junction of the first and second metatarsal bones
GB12/Wangu (Affected side)	In the posterior and inferior depression of the mastoid process behind the ear
ST7/Xiaguan (Affected side)	On the face, anterior to the ear, in the depression between the zygomatic arch and the condyloid process of the mandible
SI18/Quanliao (Affected side)	In the lower margin depression of zygomatic bone
LI20/Yingxiang (Affected side)	Next to the ala of the nose
BL2/Cuanzhu (Affected side)	On the medial end of the eyebrow
SJ23/Sizukong (Affected side)	In the depression of the tail of the eyebrow
ST4/Dicang (Affected side)	Outside the corner of the mouth, just below the pupil

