### Local reactions

Minor bleeding at the needle point.

Subcutaneous bruise.

Subcutaneous haematomas.

Pain in the operated area after operation.

Local allergy in the punctured region after treatment.

Local infection.

Local nodules.

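### The overall adverse-event comparison mixes TEA reactions with those of the shared acupuncture, which dilutes any thread effect; a comparison at the two TEA/STEA points should be added

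*Protocol article*

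**What the plan says.** The Objective section of the protocol article names both efficacy and safety of TEA against sham TEA. Under Procedure, the sham arm has the same needling at the same two points, without the thread. In both arms, "traditional acupuncture will be used as a concurrent treatment for both groups twice a week for eight weeks", with needles "retained for 30min in the following 10 acupoints". One of the two weekly acupuncture sessions follows TEA or STEA directly.

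On safety, the Adverse events section says "AEs of TEA or acupuncture will be classified as local or systemic reactions according to their location". It also has each event described by when and where it occurred, how severe it was, how it was managed and whether the patient must be withdrawn. The Local reactions list has seven types. Several could arise from either procedure, for example minor bleeding, bruising or "Local allergy in the punctured region after treatment". Nodules are more naturally linked to the thread.

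The section on data processing and statistical analysis says "The incidence of adverse events will be determined and compared between the two groups for safety outcomes". It does not say at what level (any event, class, type or site).

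**The concern.** The only feature that separates the arms is the thread at two points, yet the one stated grouping of events joins TEA and acupuncture. Location is recorded, but the only use stated for it is the local/systemic split.

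If the safety result is given as overall incidence, most of the punctures behind it have nothing to do with the randomised contrast. A real excess of thread reactions could then appear as a small difference between two similar proportions and be reported as comparable safety. That bears directly on half of the stated objective.

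**Working it through.** **Arm size (the plan's own figure).** The Sample size section gives SD 23.30, difference 21.54, alpha 0.05, power 0.90 and 10% dropout. 2 × 23.30² × (1.960 + 1.282)² / 21.54² = 24.6, rounded up to 25; 25 / 0.9 = 27.8, rounded up to 28 per arm. This matches the stated 28, which is used below.

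**Insertions per patient.**
- Acupuncture (Table 1): 8 affected-side points × 1 needle + 2 bilateral points (LI4, LR3) × 2 needles = 12 needles per session. Twice a week for 8 weeks is 16 sessions, so 12 × 16 = 192.
- TEA/STEA (Procedure): 2 points × 8 weekly sessions = 16, taking one insertion per point.
- Total 208; acupuncture is 192/208 = 92% of insertions.

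**Dilution formula.** Let b be the risk of at least one reaction from sources common to both arms, and t an independent thread-specific risk in the TEA arm. Sham risk = b. TEA risk = 1 - (1-b)(1-t). Difference = (1-b)t.

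**Numbers put in.** The article gives no reaction rates, so the following are assumptions: the same chance p for every puncture, independent punctures, and t = 20%. For any local reaction, b = 1 - (1-p)^208. For reactions at the two TEA/STEA points only, b = 1 - (1-p)^16.

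| p per puncture | Any local reaction, sham vs TEA | Difference (points) | TEA/STEA points only, sham vs TEA | Difference (points) |
|---|---|---|---|---|
| 0.05% | 10% vs 28% | 18.0 | 1% vs 21% | 19.8 |
| 0.1% | 19% vs 35% | 16.2 | 2% vs 21% | 19.7 |
| 0.5% | 65% vs 72% | 7.1 | 8% vs 26% | 18.5 |
| 1% | 88% vs 90% | 2.5 | 15% vs 32% | 17.0 |
| 2% | 98.5% vs 98.8% | 0.3 | 28% vs 42% | 14.5 |

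**Sensitivity of the two comparisons.** Power of Fisher's exact test, two-sided 0.05, 28 per arm, same assumptions on p:

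| p per puncture | t = 20%: overall vs TEA/STEA points | t = 30%: overall vs TEA/STEA points |
|---|---|---|
| 0.05% | 27% vs 47% | 57% vs 85% |
| 0.1% | 19% vs 44% | 41% vs 81% |
| 0.5% | 5% vs 30% | 9% vs 62% |
| 1% | 1% vs 22% | 2% vs 47% |
| 2% | about 0% vs 14% | about 0% vs 29% |

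The site-specific comparison is the more sensitive at every rate tried. For t = 10% with no background at all, power is only about 6%.

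**The case against.** A reader might infer that acupuncture reactions swamp any thread-specific harm, or that the safety comparison is biased. The article does not support either reading.

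- **No confounding.** Both randomised arms have the same acupuncture schedule. The shared background shrinks a difference in overall incidence; it does not distort the comparison in favour of one arm.
- **More is recorded than the local/systemic class.** Location, timing, severity and named reaction types are all captured, and a type such as nodules can be compared by arm on its own. By location, 64 of the 192 acupuncture needles (LI4, LR3) are in the hands and feet, and 32 (GB20, GB12) are at the neck and behind the ear. Half are therefore readily told apart from the TEA points.
- **No single pooled proportion is specified.** The analysis section speaks of incidence only, and comparison by type or site is not ruled out. Table layout may be set out in a fuller protocol or analysis plan that is not shown.
- **The size rests on assumptions.** At 0.05% per puncture the dilution is slight (18.0 against 19.8 points). Equal risk per puncture is also doubtful: the acupuncture needle is 0.25 mm and goes to 5 mm depth, while the TEA device uses a 0.7 mm hypodermic needle passed transversely in the muscle layer. So 92% is a share of insertions, not of reactions. Clustering of reactions within susceptible patients would also lower b.

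These points stand and limit the claim. They do not remove it. The text does state a joint classification and does not use location to isolate the sites where the arms differ. The gain from doing so has the same direction at every rate tried.

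**Conclusion.** The point holds as one of dilution. The insertion count of 192 against 16 follows from the article. An overall comparison of adverse-event incidence would show a thread effect of (1-b)t instead of t. With a 20% thread reaction and 0.05% to 2% per puncture, the overall difference runs from 18 down to 0.3 points, against 20 down to 14 points at the TEA/STEA points. All these rates are assumed, as are independence and equal risk per puncture, so the true loss could be small or large.

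Separation by site does not solve the problem of size. With 28 per arm, a 20% thread reaction has at most about 47% power at the rates tried, and rarer harms cannot be detected. Absence of significance is not evidence of equal safety under either comparison.

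**What to change.** - **Adverse events section:** code each local event, from the location and time already recorded, as at a TEA/STEA point, at an acupoint, or elsewhere.
- **Data processing and statistical analysis section:** beside the all-event comparison, add a between-arm comparison of the proportion of patients with a reaction at the TEA/STEA points, by reaction type, with confidence intervals. State that a non-significant difference will not be interpreted as equal safety.

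The cost is one coded field and one extra safety table; treatment does not change. One weakness remains. ST4 lies just outside the corner of the mouth, and the needle for point 2 enters 1 cm above a point that is itself 1 cm below the oral angle, so at about the same level. Because acupuncture follows at once on TEA/STEA days, some reactions there will be hard to assign. A rule for such cases should be fixed in advance and applied blind to arm.
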